#### Power calculations and estimation of sample size

Given that the mean SAI-E score for psychosis patients is 13/28 with a standard deviation of around 6 [32, 35], a difference of 2 points (e.g., 13 vs. 15) between groups (e.g., MCT vs. controls), which is considered to be clinically meaningful [26], is equivalent to an effect size of 0.33 with a two-tailed alpha significant level set at 5%. Under these assumptions, for reaching a sufficient statistical power of β = 80% at the end of the study, we will need *n* = 63 subjects in each arm, that is, a total sample size of *N* = 126 patients, who will be analysed at the end of the study on an intention-to-treat (ITT) basis. Attrition rates in previous RCTs investigating MCT effects on symptoms were low (approximately 10%) [18]. However, since we will follow-up patients over a more prolonged period (1 year) we have conservatively assumed a much higher drop-out rate of 50%. Under this assumption, the study will be carried out with an initial sample size of *N* = 252 patients, i.e., *n* = 126 participants in each group/arm at the study inception, which will also allow both ITT and ‘per protocol’ analyses with sufficient power. See the CONSORT flow chart in Fig. 1 for details.

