**Methods:**

This single-center, assessor-blind, parallel-group, randomised clinical trial (RCT) aims to investigate the efficacy of MCT for improving insight (primary outcome), including clinical and cognitive insight, which will be measured by the Schedule for Assessment of Insight (Expanded version) (SAI-E) and the Beck Cognitive Scale (BCIS), respectively, in (at least) *n* = 126 outpatients with SSD at three points in time: i) at baseline (T0); ii) after treatment (T1) and iii) at 1-year follow-up (T2). SSD patients receiving MCT and controls attending a non-intervention support group will be compared on insight level changes and several clinical and cognitive secondary outcomes at T1 and T2, whilst adjusting for baseline data. Ecological momentary assessment (EMA) will be piloted to assess functioning in a subsample of participants.

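### The 63 analysed patients per arm do not give the stated 80% power for a 2-point SAI-E difference: unadjusted power is about 46%, and the protocol's own inputs call for about 142 to 145 per arm

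*Protocol article*

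**What the plan says.** All of the inputs stand in the protocol article under Power calculations and estimation of sample size:

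- **Mean and SD:** "the mean SAI-E score for psychosis patients is 13/28 with a standard deviation of around 6".
- **Target difference:** "a difference of 2 points (e.g., 13 vs. 15) between groups (e.g., MCT vs. controls"), described as clinically meaningful.
- **Standardised effect and alpha:** the difference "is equivalent to an effect size of 0.33 with a two-tailed alpha significant level set at 5"%.
- **Power:** 63 per arm, 126 in total, are said to be needed on these assumptions "for reaching a sufficient statistical power of β = 80% at the end of the study". The symbol β must here mean power.
- **Dropout:** a 50% loss over one year is assumed, which doubles enrolment to 126 per arm, 252 in total. The section calls this conservative, since earlier trials of this training lost about 10%.
- **Further claim:** enrolling 252 is said to allow both ITT and per-protocol "analyses with sufficient power".

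The section also says that the 126 patients will be analysed on an ITT basis. The Statistical analysis section defines ITT as everyone with baseline data, with imputation of missing values. It plans ANCOVA on change from baseline to T1 and to T2, adjusted for baseline, and a Bonferroni correction. Neither the baseline adjustment nor the correction enters the sample size calculation.

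**The concern.** The step from d = 0.33 to 63 per arm looks wrong on sight. For a two-group comparison of means at two-sided 5% and 80% power, a required size in the low sixties per arm is the familiar answer for d = 0.50, not for one third of an SD. The effect size itself (2/6 = 0.33) is correct, and so is the dropout step (63/0.5 = 126). The error lies between them.

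At stake is the main design claim: that the trial, after the loss it plans for, can reliably detect the difference it calls clinically meaningful. The later claim about ITT and per-protocol power rests on the same 63.

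**Working it through.** **Inputs.** Difference 2, SD 6, two-sided alpha 0.05, power 0.80, 1:1 allocation, 50% dropout, all from the sample size section. No baseline-outcome correlation is given.

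**1. Trying to reproduce 63 per arm.** Normal approximation, n per arm = 2(z₀.₉₇₅ + z₀.₈₀)²/d²:

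- d = 2/6: 2 × (1.960 + 0.842)² / 0.1111 = 141.3
- d rounded to 0.33: 144.1
- d = 0.50: 2 × (1.960 + 0.842)² / 0.25 = 62.8, which rounds up to 63

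The t-test solutions are 142.2, 145.1 and 63.8. The stated figure does not reproduce, and the requirement is larger by a factor of about (0.50/0.333)² = 2.25. Other readings also fail: one-sided testing needs 112 per arm, a paired design 73, and reading 0.33 as Cohen's f about 74 to 76 in total.

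**2. Unadjusted power at 63 per arm.** The noncentrality is d × √(63/2) = 0.333 × 5.61 = 1.87. Power by noncentral t is 45.9% (45.1% with d = 0.33). The difference detectable with 80% power is 2.80 × √(2/63) × 6 = 3.0 points.

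**3. Allowing for the planned ANCOVA.** Baseline adjustment multiplies the residual SD by √(1 − r²), so the effective d is 0.333/√(1 − r²). The values of r are assumptions.

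| r | Power, 63 per arm |
|---|---|
| 0 (unadjusted) | 46% |
| 0.35 | 51% |
| 0.5 | 57% |
| 0.6 | 64% |
| 0.7 | 74% |
| 0.75 | 80% |

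The correlation needed for 80% at 63 per arm is √(1 − 63/142.2) = 0.746.

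**4. With less loss.** If all 252 are observed (126 per arm), power is 75% unadjusted and 86% at r = 0.5. With the 10% attrition of earlier trials (0.9 × 126 ≈ 113 per arm), it is 70% and 82%.

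**5. The ITT label.** One section defines ITT as all patients with baseline data, which would be the 252 enrolled. The other applies the term to the 126 left after dropout. These are different sets with different power. Imputation does not restore the outcome information lost with a dropout, so for an analysis resting on the observed SAI-E outcomes the figures for 126 fully observed patients per arm are an upper bound.

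**The case against.** The strongest reply is that 46% does not describe the planned analysis. That analysis adjusts for baseline, includes everyone with baseline data, imputes, and also tests change at T1 (about 8 weeks), where loss may be well below 50%. On favourable but not extreme assumptions, such as 10% loss and r = 0.5, power for 2 points exceeds 80%. This stands as a statement about what the trial may achieve. It does not rescue the calculation, because the section derives 63 from the raw SD, says that the number follows from the listed assumptions, and gives no correlation.

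Three stronger readings are tempting, and the documents do not support them.

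- **That the trial will more likely than not miss a 2-point effect.** This holds only for the unadjusted comparison of one-year completers. With ANCOVA, power passes one half at r of about 0.35.
- **That the abstract contradicts the 252.** It refers to "126 outpatients with SSD at three points in time", but qualifies the number as a minimum, which is compatible with enrolling 252 to retain 126.
- **That power is lower still, about 35%, because of Bonferroni.** That figure assumes an even split of alpha over two tests (0.025 each). The protocol does not say how many tests the correction covers.

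It is also only an inference that the authors used d = 0.50. The protocol mentions neither that value nor a 3-point difference, and 63 matches it by the normal approximation, whereas the t-test gives 64 (79.5% power at 63).

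**Conclusion.** The stated sample size is wrong as written. On the protocol's own inputs, 80% power for 2 SAI-E points needs about 142 to 145 analysed patients per arm. With 63 per arm, power is about 46% without adjustment, and 80% applies to about 3 points. Only the arithmetic of a two-group comparison of means is needed for this.

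The power of the planned ANCOVA is higher by an amount the protocol does not quantify. At 63 per arm it stays below 80% unless r is about 0.75. With 252 fully observed it runs from 75% (unadjusted) to 86% (r = 0.5). The trial may therefore prove adequately powered if attrition is low and the correlation moderate, but the protocol does not make that case. The sufficient-power claim for ITT and per-protocol analyses lacks support from the stated inputs, and the ITT label is used for two different sets. This should be corrected, since a definite power figure has been published that its own assumptions contradict.

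**What to change.** Revise the sample size paragraph and leave enrolment at 252:

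1. Keep 2 points as the clinically meaningful difference; do not change it to fit the number.
2. Either state that 63 analysed per arm gives about 46% unadjusted power for 2 points and 80% only for about 3 points, or state an assumed baseline-outcome correlation, justify it, and give the resulting ANCOVA power. The second is more informative because it matches the planned analysis.
3. Give separate figures for the 252 randomised (the ITT set as defined under Statistical analysis) and for the 126 expected at one year, and stop calling the latter the ITT sample.
4. Remove the sufficient-power claim for the per-protocol set, or recompute it for the size that set is expected to have.
5. If a Bonferroni-adjusted power is quoted, state the number of tests it assumes.

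The cost is one rewritten paragraph and a less favourable stated power. No extra patients are needed and no trial procedure changes.

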## Discussion

### Relevance and impact

This is the first large RCT testing the long-term effects of group MCT on clinical and cognitive insight in addition to several relevant clinical outcomes in a representative sample of patients with schizophrenia spectrum disorders. Although MCT has been consistently demonstrated to improve positive symptoms [14–18], the benefits of MCT on insight are yet to be established [3], which is of major clinical relevance given the association of insight with outcomes in schizophrenia and related disorders [2]. This is supported further by three previous trials which revealed other non-MCT metacognitively oriented treatments to have a positive impact on insight [20–22].

The clinical relevance will be immediate in raising clinicians’ awareness of insight, particularly regarding its role in clinical outcomes. In addition, this RCT will add to the field by showing the possibility of improving insight through an eassily applicable intervention such as MCT, which represents a more patient-centred treatment approach.

### Outcome measures

In addition to the primary outcome of this RCT, namely insight, we will consider several clinical outcomes, both positive and negative, such as symptom severity, functioning, readmissions and suicidal behaviour, thus testing the so-called ‘Insight Paradox’ [54]. Although the positive impact of MCT on symptoms has been established [14–18], most of previous RCTs included in these meta-analyses compared MCT with TAU. Therefore, not only this RCT may replicate this, but also by comparing the MCT group with an active intervention control group, if the above positive effect was shown, this would provide further support for the benefits of MCT on symptoms. Beyond and above the effects of MCT on symptoms, functioning will be comprehensively examined, consistently with current guidelines focused on recovery as main outcome measure [55]. Also, functioning will be evaluated with novel methodology such as EMA, which has not been sufficiently researched in psychosis patients.

However, insight was also linked with negative outcomes. In particular, insight was thought to lead to depression, hopelessness and suicidality, which is known as the demoralization syndrome [56, 57] or ‘Insight Paradox’ [54]. However, recent research did not show a ‘direct’ relationship between insight and suicidality in first-episode psychosis, which was due to the confounding effects of previous suicide attempts and depression on such an association [32]. The question therefore arises, i.e., whether an insight improving intervention (such as MCT, which is to be tested in this trial) may reduce suicide risk (and improve mood) in psychosis, which will be properly investigated in this RCT. In addition to suicidal behaviour-related outcomes, we will test whether MCT can reduce admissions over the trial period, which is of relevance from a cost-effectiveness perspective [58].

### Methodological issues

Insight, which is the primary outcome of the study, will be measured with the multidimensional SAI-E scale [26] based on the multidimensional David’ model of insight [23]. This will allow us to look at the effects of MCT on insight dimensions individually, which may differ.

Recruitment and retention of patients in psychosis research is challenging, particularly in long-term studies. Accordingly, given our 1-year follow-up study period we have decided to invite all those potentially eligible patients who are seen at our clinic during the 6-month enrolment period. This approach has, of course, strengths and weaknesses. On the one hand, the sample will be very likely to be representative of the local population of psychosis patients, most of whom are, to some degree, chronic (rather than early-onset psychosis patients). On the other hand, the inclusion of chronic patients may reduce the room for improvement. However, it is precisely this group of patients, which tends to be relatively neglected by research and stakeholders in comparison with first-episode patients, who may particularly benefit from receiving MCT. Moreover, this design will allow us to examine whether chronicity, including (mild) cognitive impairment, mediates the response to MCT, i.e., by comparing response to MCT (in comparison with controls) in chronic and early-onset patients. Nevertheless, those with an IQ ≤ 70 will be excluded from the study.

Unlike most of previous studies, both controls and the intervention group (MCT) will attend similar weekly group sessions at the clinic with support from the clinical team, thus minimising stigma-related issues. When designing the study with an active control group, we were aware that we were reducing the room for improvement, that is, the likelihood of finding between-group differences in terms of insight and the other secondary outcomes of interest, namely symptom severity, admissions, suicidal behaviour and functioning. However, this design will represent a more challenging test for MCT to demonstrate whether it should be incorporated into routine clinical practice and guidelines. Thus, this approach will make the trial more similar to our routine practice since patients regularly attend psychoeducation-like/supportive groups at our clinic at staff (psychiatrists and psychologists) discretion on the basis of regular individualised needs assessments, which may also maximise completion rates among controls. Nevertheless, participants will be reminded via mobile text message their next group appointment within the previous 24 h. In addition, it is worth noting that from an ethical perspective, although controls will be prevented from receiving MCT, at least they will be able to attend a weekly supportive group at the outpatient clinic, from which they may benefit in addition to their treatment as usual.

With regard to the statistical analyses, two points deserve some comment. First, the effect of variables changes over time on outcome measures will be considered since survival analyses will be performed. Second, by using path analysis we will be able to better understand the causality relationships between the variables tested in the models, which is what really matters. In addition, devising new dynamic probabilistic models to extract knowledge in the form of digital biomarkers obtained jointly from the patient’s EMA and electronic health records should contribute to paving the way towards the so-called personalized medicine.

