Clinical and cognitive insight are different, albeit related, concepts [2, 12]. There has been a growing interest in clinical insight in psychosis since the multidimensional model of insight proposed by David [23], which encompasses three different, albeit overlapping, dimensions - illness recognition, symptom relabelling and treatment compliance – and has been consistently replicated ever since [24]. Multidimensional measurement scales, such as the Scale of Unawareness of Mental Disorder (SUMD) [25] and the Schedule for Assessment of Insight (SAI-E) [26], were also devised for research. Cognitive insight is a core metacognitive domain which refers to the person’s ability to evaluate and correct his/her own distorted beliefs and misinterpretations (self-reflectiveness) and the tendency to overconfidence in one’s conclusions (self-certainty) [10].

The ***main aim*** of this RCT is to test whether MCT can improve insight, including clinical and cognitive insight, in patients with schizophrenia over a 1-year follow-up. As ***secondary aims,*** we will investigate the effect of MCT-related insight changes on clinical outcomes, including symptomatic severity, hospitalizations, suicidal behaviour and psychosocial functioning. In addition, we will pilot the use of ecological momentary assessment (EMA) via two web-based applications - www.MEmind.net [27] and the Evidence-Based Behaviour platform eB2 app [28] - to measure functioning in a subsample of participants.

Specifically, the following five hypotheses are to be tested: i) that MCT will result in higher cognitive and clinical insight levels and that MCT-induced insight improvement will be linked with ii) reduced symptom severity and iii) hospitalizations, iv) lower suicide rates and v) better functioning than in controls.

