### Recruitment process

Recruitment will occur at the outpatient clinic known as Centro de Salud Mental de Arganzuela at which two consultant psychiatrists ([name], [name]) and one consultant psychologist ([name]) will refer potential candidates to the principal investigator of the project ([name]) to arrange a first pre-recruitment interview during which the relevant information of the project is explained to the candidate in lay terms, including an information leaflet. Those agreeing to participate in the study are screened against the above inclusion/exclusion criteria at this point. Those who are found to fulfill the study selection criteria undertake a neurocognitive assessment. Specifically, the WAIS-IV [30] is administered by a MSc-level clinical psychologist ([name]) in order to rule out an IQ ≤ 70, which is an exclusion criterion. Those with an IQ > 70 are administered the Trail Making Test (TMT) [31], which assesses executive function and has been found to correlate with insight scores in psychosis patients [32], by [name] shortly after the WAIS-IV in order to complete the baseline neurocognitive assessment at this point.

After a short break of around 5 min, [name] performs the MINI [29] to confirm the diagnosis of psychosis and conducts the psychopathological, insight, metacognitive and functioning assessments detailed below. Also, a set of demographic and clinical variables, which are listed below, are collected at this baseline interview.

All participants will be encouraged to continue taking medication as prescribed by the treating consultant psychiatrist, usually antipsychotics, and to receive non-metacognitive oriented psychotherapy, such as psychoeducation. There will be no restrictions on medication changes over the trial, which can be made by the treating consultant at any time, although medication-related variables will be considered in secondary analyses as potential mediators/confounders. Participants are informed of their right to drop out of the study at any time without having to disclose a specific reason, which will have no implications on treatment or service provision. Participants are not compensated with any amount of money for completing the assessments and/or receiving the interventions, namely MCT or attending a weekly support group.

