### Outcome measures

#### Co-primary outcomes

Insight is the primary outcome of this RCT and both clinical and cognitive insight will be considered.
*Clinical insight* will be measured with the Spanish version [33] of the Schedule for Assessment of Insight, expanded version (SAI-E) [26]. The SAI-E takes the form of a semi-structured interview which enquires about different aspects of insight and provides scores on three insight dimensions in line with David’s model [23] - illness recognition, symptom relabeling, treatment compliance - and a total insight score. The scale was found to be easily applicable in routine clinical practice [34] and good to excellent inter-rater reliability was reached, with total insight scores intra-class correlations coefficients ranging from 0.92 to 0.98 (*p* < 0.001) [35]. [name] received training from the scale author ([name]) and they both co-led the validation study of the SAI-E Spanish version [33], which will be used in this RCT.*Cognitive insight* will be assessed by the Spanish version [36] of the Beck Cognitive Insight Scale (BCIS) [10], which is a 15-item self-administered scale which evaluates self-reflectiveness (9 items) and self-certainty (6 items). A composite index can thus be calculated by subtracting self-certainty from self-reflectiveness. Internal consistency was found to be acceptable (Cronbach’s α = 0.60–0.68) [37].

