Finally, variables inter-relationships over the trial period will be examined by means of path analysis through structural equation modeling, thus testing the effect of putative mediators/moderators/confounders/covariates, including neurocognition measures, on the above associations.

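### The insight-to-outcome part of hypotheses ii–v is read causally from a path analysis, but insight change is not randomised, so a poorly measured shared cause can make insight look effective when it is not

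*Protocol article*

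**What the plan says.** The Background states the secondary aim as causal: "we will investigate the effect of MCT-related insight changes on clinical outcomes". Its hypotheses ii–v follow the same line: "MCT-induced insight improvement will be linked with ii) reduced symptom severity and iii) hospitalizations, iv) lower suicide rates and v) better functioning than in controls".

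The tool for the mechanistic part comes last in Statistical analysis: "variables inter-relationships over the trial period will be examined by means of path analysis through structural equation modeling". Putative mediators, moderators, confounders and covariates are to be tested there together. Under Methodological issues the Discussion then says: "by using path analysis we will be able to better understand the causality relationships between the variables tested in the models, which is what really" (cut before its last word).

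Other statements bear on this point:

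- Randomisation and assessor-blindness: participants are allocated to MCT or the support group. Nothing else is randomised.
- Statistical analysis: symptoms and functioning are compared between arms by ANCOVA. Suicidal events and admissions are modelled by Cox regression with baseline adjustment.
- Recruitment process: "There will be no restrictions on medication changes over the trial". The same sentence goes on to say that medication-related variables will be considered in secondary analyses as possible mediators or confounders. Strengths and weaknesses repeats that commitment.
- Co-primary outcomes: the SAI-E gives scores on "illness recognition, symptom relabeling, treatment compliance - and a total insight score". The BCIS covers self-reflectiveness and self-certainty.
- Discussion, Outcome measures: an earlier association between insight and suicidality is attributed to confounding by previous attempts and depression.

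**The concern.** Randomisation protects two of the three links in the mediation chain: MCT to insight, and MCT to outcome. It does not protect insight to outcome. The path coefficient for that link tests a partial association given the measured variables. This equals an effect of insight only if nothing unmeasured, or badly measured, moves both insight change and outcome change.

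The article itself points to a candidate. Medication may change during follow-up, and treatment compliance is one of the SAI-E dimensions. A patient whose adherence improves for any reason may score higher on insight and also have fewer symptoms, without greater awareness of illness playing any part. The article knows that this link can be confounded, since it says so of the earlier suicidality finding. It states no such limit for its own path analysis.

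At stake is the mechanistic conclusion. The trial could report that raising insight improves clinical outcomes when insight does nothing to them.

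**Working it through.** The article gives no figure for this path, so there is none to reproduce. The size below is an illustration under stated assumptions.

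**Inputs from the article (Power calculations and estimation of sample size).** SAI-E difference 2, SD 6, so d = 2/6 = 0.33. Two-sided alpha is 5%. The article plans 126 patients at study end and 252 enrolled.

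**Assumed inputs.** One shared cause U has standardised loading g on both insight change M and outcome change Y, and no adjustment is made for it. The true effect of insight on Y and the true effect of MCT on Y are both zero. Y is continuous. With T the arm (0 or 1):

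- M = 0.33·T + g·U + √(1 − g²)·e₁
- Y = g·U + √(1 − g²)·e₂

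**Expected bias.** Given the arm, M and Y each have variance 1 and covariance g². The path coefficient of Y on M therefore has expectation g², not 0. This is 0.09 at g = 0.3 and 0.25 at g = 0.5. The spurious indirect effect is 0.33 × g², that is 0.03 SD and 0.08 SD.

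**Closed-form check of the insight-to-outcome path at N = 126.** By Fisher's z with one conditioning variable, the standardised shift is √(N − 4) × atanh(g²).

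- g = 0.3: √122 × 0.0902 = 0.997. The rejection rate is P(Z > 1.96 − 0.997) plus the small opposite tail, about 17%.
- g = 0.5: √122 × 0.2554 = 2.821. The rejection rate is P(Z > 1.96 − 2.821), about 81%.

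**Both legs significant at N = 126.** The MCT-to-insight leg has shift (1/3) × √(126/4) = 1.871 and power of about 46%. Multiplying gives 0.464 × 0.169 = 0.08 and 0.464 × 0.805 = 0.37. (That 46% is well below the 80% stated for 63 per arm is a separate matter. This point does not depend on it.)

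**Simulation.** Two independent sets of 4,000 trials per setting, using OLS of M on T, Y on T and M, and Y on T, gave:

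| | g = 0 | g = 0.3 | g = 0.5 |
|---|---|---|---|
| Insight-to-outcome path, N = 126 | 4.9–5.4% | 17.4–18.2% | 80.8–80.9% |
| Both legs, N = 126 | 2.1% | 7.7–7.9% | 36.1–37.1% |
| Insight-to-outcome path, N = 252 | 4.7–4.8% | 28.5–29.3% | 97.8–98.2% |
| Both legs, N = 252 | 3.8% | 20.9–22.5% | 72.8–74.1% |

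Single figures come from one set only. The arm contrast on Y stayed near 5% in every setting. The N = 252 rows assume that all enrolled patients are followed to the end. A larger sample makes the false finding more likely, because the bias does not shrink with N.

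**What adjustment achieves.** With U itself in the model, the path test returns to about 5%. With a proxy of U of reliability 0.5 at N = 126, it rejects in 8.5% at g = 0.3 and 35.4% at g = 0.5. The closed form agrees. At g = 0.5 the residual correlation is 0.125/0.875 = 0.143, the shift is √121 × atanh(0.143) = 1.58, and the rate is about 35%.

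**The case against.** The other side has a substantial case.

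- **Medication is not ignored.** A reader who stops halfway through the sentence in Recruitment process might infer that it is. The rest of the sentence, Statistical analysis, and Strengths and weaknesses all commit to modelling medication variables or confounders. This stands. It limits the concern to causes that are unmeasured or poorly measured. In the text shown, medication is listed only as current medications at baseline, and no adherence measure outside the SAI-E is described. The assessment table is not visible, so one may exist.
- **Hypotheses ii–v do not rest wholly on the path model.** A reader might infer that all four fall with it. They end in a comparison with controls, and the ANCOVA and Cox models test the same outcomes between arms. Those tests are valid, and a null MCT effect would be visible beside any path result. Only the credit given to insight depends on the path analysis.
- **The wording is moderate.** The hypotheses speak of a link, and the Discussion speaks of better understanding causality, not of proving it. This is fair, but the aim is still worded as an effect of insight changes, and the Discussion still gives the path model a causal reading.
- **Compliance can be separated.** It is scored as its own SAI-E dimension, subtotals are analysed, and the BCIS as described has no compliance component. The article does not say which insight score enters the model, so it cannot be assumed that the total is the mediator.
- **The magnitude uses an assumed g**, equal on both sides and unadjusted, and a continuous outcome. Two of the outcome domains are time-to-event, and the rates do not carry over to them directly.
- **Mediation detail belongs in an analysis plan.** That is true, and its absence here is no finding. The point concerns what the article states, namely a causal reading that the design does not secure.

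**Conclusion.** The point holds in a limited form. The arm comparisons support causal conclusions about MCT. The insight-to-outcome paths do so only if no shared cause of insight and outcome is left unmeasured or badly measured, and the article gives those paths a causal reading without that condition.

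The size depends on the assumed g. With no adjustment at N = 126, false significance of the path runs from about 17–18% (g = 0.3) to 81% (g = 0.5), and of both legs together from about 8% to 36–37%, against a nominal 5%. Good adjustment brings the path back to about 5%, and poor adjustment does so only in part. The documents do not show that a false mediation finding will occur, only that it can.

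**What to change.** In Statistical analysis and in Methodological issues:

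1. State that causal conclusions for ii–v are limited to the MCT-versus-control comparisons.
2. Report insight-to-outcome and indirect paths as exploratory and conditional on no unmeasured confounding of insight and outcome. Reword the sentence on causality to match.
3. Report each indirect effect with a sensitivity analysis over the residual correlation between the insight and outcome equations, and give the value at which the effect disappears. No fixed pass mark is needed.
4. As a sensitivity analysis only, repeat the model with the SAI-E illness-recognition and symptom-relabelling scores and the BCIS in place of the SAI-E total. Making this the main model would be a trade-off. It departs from the three-dimensional concept of insight that the trial adopts, and it would discard part of the effect if MCT improves compliance through insight.

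The cost is new wording and a little more analysis of data already planned, with no extra patients or assessments. The price is a weaker mechanistic claim.
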